#### Microbiota analysis

Clinical skin and intestinal flora DNA will be analyzed using 16S rDNA amplicon sequencing to determine the microbial composition of the samples. 16S rRNA gene sequencing will be performed using Novogene (Beijing, China), according to the manufacturer’s instructions. Raw data obtained by sequencing will then be spliced and filtered to obtain clean data. The DADA2 method will be employed to reduce noise based on the effective data, and sequences with abundances <5 will be filtered out to obtain the final amplicon sequence variants (ASVs).

For the ASVs obtained, species annotation will be performed on representative sequences to obtain the corresponding species information and abundance distribution. Simultaneously, the abundance, alpha diversity calculation, Venn diagrams, and petaline graphs of ASVs will be analyzed to obtain species richness and evenness information. Additionally, multiple sequence alignment of ASVs will be carried out to construct a phylogenetic tree. Principal coordinate analysis (PCoA), principal component analysis (PCA), nonmetric multi-dimensional scaling (NMDS), other dimension reduction analysis, and sample phylogenetic tree display will be applied to explore the differences in community structure between CSU patients and healthy people, and between the acupuncture group and sham acupuncture group. To further explore the community structure differences among grouped samples, statistical analysis methods, including *t*-test, MetaStat, and LEfSe, will be employed to test the significance of species composition and community structure of grouped samples.

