## Methods and analysis

### Study design

This is a parallel randomized sham-controlled functional neuroimaging study. Fifty CSU patients and 25 matched healthy subjects will be randomly assigned to the verum or sham acupuncture groups at a 1:1 ratio. The total observation period of this study is 6 weeks, including a baseline period of 2 weeks and a clinical treatment period of 4 weeks. Before treatment, all participants (*n* = 75) will undergo clinical index evaluation, magnetic resonance scanning, and microflora collection. Following treatment, only the CSU patients will be reassessed for these indicators. The study flow chart is presented in Figure 1, and the schedule of enrolment, interventions, and assessments is shown in Table 1. This trial will be reported following the Standard Protocol Items: Recommendations for Interventional Trials (SPIRIT).

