**Assessments**				
UAS7/VAS		√	√	√
PSQI/DLQI		√	√	√
HAMA/HAMD		√	√	√
SAS/SDS		√	√	√
Skin wheal measures		√	√	√
IgE/CRP		√		√
fMRI		√		√
Gut/skin microbiota		√		√

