### Randomization and blinding

Eligible patients will be randomly assigned to the acupuncture or sham acupuncture group at a 1:1 ratio. Statistical analysis will be performed using SPSS software (version 22.0) to generate random sequences with a random number table. The random distribution cards will contain random numbers, serial numbers, and groups, packed in opaque numbered envelopes. The envelope will be unsealed following study enrolment. Owing to the particularity of acupuncture research, it is difficult to blind the acupuncture operators. As such, fake acupuncture devices and separate treatment rooms will be used for each patient to blind them as much as possible. Moreover, the “three separations strategy” will be strictly adhered to by researchers, operators, and statisticians throughout the research process. Efficacy evaluation, data analysis, and statistics will be completed by third parties blinded to the groupings.

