### Sample size

Due to the particularity of the neuroimaging mechanism, the clinical sample calculation method is not applicable. According to fMRI sample size research, each group should include at least 6–12 patients (40), while the statistical data of 20 subjects resembles that of large sample data for 130 subjects (41). Considering the uncertain factors in this study, including the loss or elimination of subjects and unavailable data due to head movements, we included 50 patients and 25 matched healthy persons in this study.

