#### Correlation analysis

The interactions between brain functional connectivity, microbiota, and clinical indicators in patients will be analyzed using MATLAB (version R2015b), which will calculate the Spearman correlation. An effect size of *r* = 0.10 is considered small (explained by 1% variance), 0.30 is medium (explained by 9% variance), and 0.50 is large (explained by 25% variance). The *Z* test and Fisher’s r-to-z transformation will be used to evaluate the differences in correlation coefficients between the acupuncture and sham acupuncture groups. Statistical significance is set at *p* < 0.05. Cytoscape (v. 3.8.2) will be employed to construct a visual network of interactions between brain functional connectivity, microbiota, and clinical indicators.

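### The acupuncture-versus-sham microbiota test fixes neither the visit nor any use of each patient's week 0 sample; adjusting for that sample is a nearly free gain in precision

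*Protocol article*

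**What the plan says.** **Sampling.** The Assessments block of Table 1 ticks the row "Gut/skin microbiota" at week 0 and at week 4. The Study design section adds: "Following treatment, only the CSU patients will be reassessed for these indicators". Each patient therefore gives two samples per body site, and each healthy control gives one.

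**Allocation and size.** "Eligible patients will be randomly assigned to the acupuncture or sham acupuncture group at a 1:1 ratio" (Randomization and blinding). The Sample size section states that "we included 50 patients and 25 matched healthy persons in this study".

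**Analysis.** The Microbiota analysis section sets out to explore "differences in community structure between CSU patients and healthy people, and between the acupuncture group and sham acupuncture group". It then lists a t-test by name and continues: "MetaStat, and LEfSe, will be employed to test the significance of species composition and community structure of grouped samples". The list is introduced as open-ended, and the type of t-test is not given. The section does not say which visit enters the comparison of the two arms, whether change is analysed, or how a patient's two samples are linked. It gives no significance level of its own; the Correlation analysis section has "Statistical significance is set at *p* < 0.05".

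**The concern.** One list of tests serves two comparisons with different data structures. Patients against healthy controls at baseline has one sample per person, and group tests suit it as listed. The second contrast, "and between the acupuncture group and sham acupuncture group", draws on patients who were each sampled twice, and nothing in the text tells the analyst what to do with the second sample.

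Two things are at stake. The first is precision. A test on week 4 samples alone leaves out a pre-treatment measurement that has already been collected, in a trial with only 25 patients per arm. The second is an open choice. Because the visit is not fixed, an analyst could choose it after seeing the data, or could place all samples from an arm in one group. The treatment effect on the microbiota is part of the brain-gut-skin mechanism that the Discussion sets out, so the between-arm test deserves a fixed form.

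**Working it through.** The article states no power, effect size, SD or within-patient correlation for the microbiota, so there is no figure of its own to reproduce.

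**Inputs from the article**
- 50 patients at 1:1, so 50 / 2 = 25 per arm.
- Two samples per patient and site, so 25 × 2 = 50 samples per arm and site.

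**Assumptions, not in the article**
- Two-sided level 0.05 for the microbiota tests.
- Correlation ρ between a patient's week 0 and week 4 values of 0.3 to 0.8.
- A week 4 effect of d = 0.6 SD.
- One approximately normal feature, such as an alpha-diversity index, with equal variance at both visits and no dropout.

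**Step 1. Week 4 only, against week 4 adjusted for week 0**

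With n per arm, the expected test statistic is d√(n/2) for week 4 alone. Adjustment for week 0 multiplies the residual variance by 1 − ρ², so the statistic becomes d√(n/2) / √(1 − ρ²).

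Week 4 alone: 0.6 × √12.5 = 2.121. The normal approximation to power is Φ(2.121 − 1.960) = 0.56. Simulation with t-tests (20,000 replicates) gives about 0.55.

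| ρ | 1 − ρ² | Expected statistic, adjusted | Power, normal approx. | Power, simulated |
|---|---|---|---|---|
| 0.3 | 0.91 | 2.224 | 0.60 | about 0.58 |
| 0.5 | 0.75 | 2.449 | 0.69 | about 0.67 |
| 0.7 | 0.51 | 2.970 | 0.84 | about 0.82 |

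Expressed as sample size, a week 4-only test would need 25 / (1 − ρ²) patients per arm to match the adjusted analysis: about 27, 33 and 49 at the three correlations.

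The effect detectable with 80% power does not depend on the assumed 0.6 SD. It is √(2/25) × (1.960 + 0.842) = 0.79 SD for week 4 alone. Multiplied by √(1 − ρ²), it falls to 0.76, 0.69 and 0.57 SD.

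**Step 2. Validity of week 4 only**

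With no true effect, the simulated rejection rate of the week 4-only test lies between 0.047 and 0.053 over ρ = 0.3 to 0.8. The level is held, and the only cost is precision.

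**Step 3. What stacking both visits would do**

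Treating 50 samples per arm as independent gives the arm mean a nominal variance of σ²/(2n). The true variance is σ²(1 + ρ)/(2n). The true two-sided level is therefore 2[1 − Φ(1.960 / √(1 + ρ))].

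| ρ | 1.960 / √(1 + ρ) | Level, formula | Level, simulated |
|---|---|---|---|
| 0.3 | 1.719 | 0.086 | 0.084 |
| 0.5 | 1.600 | 0.110 | 0.108 |
| 0.7 | 1.503 | 0.133 | 0.134 |
| 0.8 | 1.461 | 0.144 | 0.151 |

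Pre-treatment samples carry no treatment effect, so stacking also halves the contrast. Simulated power for the 0.6 SD effect drops to 33–36%, despite the inflated level.

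**Step 4. Adjustment or change score**

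A test on change has residual variance factor 2(1 − ρ), which exceeds 1 when ρ is below 0.5. For an effect of 0.8 SD at ρ = 0.3, power is 0.67 for change, 0.81 for week 4 alone and 0.84 for the adjusted analysis. Adjustment is the safer choice when ρ is unknown.

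**The case against.** A reader might infer that the listed tests treat every sample as independent and count each patient twice. The text does not say so. The list is open, the t-test type is not named in this section, and grouping samples does not mean stacking visits. The same t-test could also be run on each patient's change, which would keep the pairing. The figures in Step 3 therefore describe a possibility that the wording leaves open, not a planned analysis. Nor is an independent-samples test of week 0 against week 4 within an arm planned anywhere.

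A reader might also infer that a week 4 comparison misses the trial's target. It does not. Under randomisation, the expected difference between arms at week 4 equals the expected difference in change.

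Three further points count against the concern. The section presents this work as exploratory, and the primary outcome is the UAS7, not the microbiota. The article condenses a fuller protocol, and an analysis plan that is not shown may already name the visit and the baseline term. The size of the gain rests on an assumed correlation and effect; at ρ = 0.3 it is only about 3 percentage points of power. The calculation for one normal feature also does not show how MetaStat or LEfSe would behave on sequencing abundances.

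All of this stands. It removes any charge of error. It does not change the fact that the section names contrasts and tests while making no stated use of a baseline sample that the trial collects.

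**Conclusion.** This is a free or cheap improvement, not an error in the stated plan. The Microbiota analysis section leaves the visit and the week 0 sample unaddressed for acupuncture versus sham. Read as a week 4 comparison, the analysis is valid but less precise than the collected data allow. The gain from adjustment is small at a correlation of 0.3 (power about 55% to 58%) and material at 0.5 (67%) or 0.7 (82%), given 25 per arm, an assumed 0.6 SD effect, a two-sided 0.05 level and a roughly normal feature. A fixed rule would also exclude stacking both visits, which the document does not propose but which would carry a false-positive rate of about 9–15%.

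**What to change.** In the Microbiota analysis section:

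- State that the acupuncture-versus-sham test uses one value per patient: the week 4 value (alpha diversity or transformed taxon abundance), modelled on arm and the same patient's week 0 value.
- For community structure, test the arm-by-visit term by permuting arm labels between whole patients, so that a patient's two samples stay together.
- Keep MetaStat and LEfSe for comparisons with one sample per person, such as patients at week 0 against healthy controls.

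The cost is a few sentences and a little more programming; no extra patients or samples are needed. The one drawback is that patients without a week 0 sample drop out of the adjusted model, unless a mixed model with a patient effect is used.

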#### Correlation analysis

The interactions between brain functional connectivity, microbiota, and clinical indicators in patients will be analyzed using MATLAB (version R2015b), which will calculate the Spearman correlation. An effect size of *r* = 0.10 is considered small (explained by 1% variance), 0.30 is medium (explained by 9% variance), and 0.50 is large (explained by 25% variance). The *Z* test and Fisher’s r-to-z transformation will be used to evaluate the differences in correlation coefficients between the acupuncture and sham acupuncture groups. Statistical significance is set at *p* < 0.05. Cytoscape (v. 3.8.2) will be employed to construct a visual network of interactions between brain functional connectivity, microbiota, and clinical indicators.

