##### Inclusion criteria

The study will enroll patients who meet the following criteria (1) meet the diagnostic criteria of CSU as defined in “The international EAACI/GA^2^LEN/EuroGuiDerm/APAAACI guideline for the definition, classification, diagnosis, and management of urticaria” (2); (2) right-handedness of either sex, aged between 18 and 70 years, with a minimum of 6 years of education; (3) urticaria activity score 7 (UAS7) > 14; (4) no metal implants, no fMRI scanning contraindications; (5) patients who have not taken any antihistamines within 2 weeks before entering the study, and have not used steroid hormones or immunosuppressants within the last month; (6) no acupuncture treatment within 3 months before entering the study, no participation in other ongoing clinical studies; (7) and patient who have provided signed informed consent and volunteered to participate in this study.

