Given the complexity of CSU pathogenesis, it is not sufficient to explore its mechanism using a single peripheral or central mechanism. Moreover, due to the overall regulatory characteristics of acupuncture, it is difficult to systematically explain the acupuncture treatment mechanism of CSU from a single perspective. Nevertheless, gut microbiota is significantly associated with multiple brain network functional connections, including DMN (44). Hence, this study will exploit the key brain networks of CSU as a breakthrough point to explore the acupuncture treatment mechanism for CSU in the “brain-gut-skin” context. Compared to previous acupuncture central mechanism studies for CSU treatment that only focused on single brain regions, we will explore the mechanism using rsFC, dFC, and microstate extraction to evaluate brain function while combining microbiota and clinical symptom index correlation analyzes. Hence, this study is expected to provide scientific and objective visual evidence for the clinical application of acupuncture in CSU treatment and promote further development of basic research on CSU treatment.

This study has certain limitations. First, the acupuncturists cannot be blinded due to the particularity of the acupuncture procedure, which may cause bias. Second, because of the skin sensitivity of patients with CSU, the blunt needles used in the sham acupuncture group may stimulate the patients’ skin, resulting in unpredictable changes in the neuroendocrine network, which may affect the experimental results. Third, as a single-center study, the number of samples will be small, and the results may not be extrapolated owing to the single operator, research equipment, and inclusion of patients.

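### The brain–microbiota–symptom network rests on Spearman correlations with no adjustment for age or sex, so an edge can reflect shared dependence on either

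*Protocol article*

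**What the plan says.** The protocol article, under Correlation analysis, states that the interactions between connectivity, microbiota and clinical indicators "in patients will be analyzed using MATLAB (version R2015b), which will calculate the Spearman correlation". The threshold follows: "Statistical significance is set at *p* < 0.05". Size labels are given for the coefficients, among them "0.30 is medium (explained by 9% variance), and 0.50 is large (explained by 25% variance". Cytoscape "will be employed to construct a visual network of interactions between brain functional connectivity, microbiota, and clinical indicators". A Z test on Fisher-transformed coefficients compares the two arms. No covariate is named in that section.

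The patient inclusion criteria admit "right-handedness of either sex, aged between 18 and 70 years, with a minimum of 6 years of education". The Sample size section gives 50 patients, which is 25 per arm at 1:1. The Discussion says the study will "explore the acupuncture treatment mechanism for CSU in the “brain-gut-skin” context".

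The only covariate regression mentioned anywhere is a step in the fMRI preprocessing list, and its covariates are not named.

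**The concern.** Entry spans 52 years of age (70 − 18) and both sexes. Resting connectivity, gut and skin flora, and sleep and mood scores could each plausibly vary with age or sex. If both members of a pair do, they will correlate across patients even when neither has anything to do with the other. A plain rank correlation cannot tell this from a direct link.

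This is bias, not chance. Multiplicity control does not remove it, and a larger sample makes it more significant. Matching the healthy controls does not help either, because these correlations are computed among patients.

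The correlation network is the only analysis described that joins the brain, microbiota and symptom findings. If some edges are age or sex gradients, reading the network as a mechanism is not secure.

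**Working it through.** **The plan's own figures.** Variance explained is r²: 0.10² = 1%, 0.30² = 9%, 0.50² = 25%. These agree with the article, which gives no other calculation for the correlations.

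**Inputs from the article.** n = 50 patients (25 per arm); ages 18–70; either sex; threshold 0.05.

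**Assumptions.**
- The test is two-sided (the section does not say).
- Each of two measures correlates at a with a common factor, and the two are otherwise independent. The article gives no value for a, so a range is shown.
- Age is uniform on 18–70. In the alternative case, the factor is sex with 70% women.

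**Spurious correlation.** With x and y each correlated a with the factor and no direct link, the expected product-moment correlation is a × a = a². This gives 0.04, 0.09, 0.16, 0.25 and 0.36 for a = 0.2 to 0.6. The rank version is slightly smaller (table).

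**Critical value.** |r| = t / √(n − 2 + t²), with t the 97.5% point on n − 2 degrees of freedom. This gives 0.279 at n = 50 and 0.396 at n = 25.

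**Partial rank correlation.** (r_xy − r_xc·r_yc) / √[(1 − r_xc²)(1 − r_yc²)], all on ranks, tested on n − 3 degrees of freedom, where c is the common factor.

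**Simulation with age as the factor, 20,000 data sets per cell:**

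| a | Mean plain Spearman, n = 50 | Plain, p < 0.05, n = 50 | Plain, p < 0.05, n = 25 | Partial given age, p < 0.05, n = 50 |
|---|---|---|---|---|
| 0 | 0.00 | 5.0% | 5.0% | 5.0% |
| 0.2 | 0.04 | 5.7% | 5.5% | 5.0% |
| 0.3 | 0.09 | 8.9% | 6.8% | 5.1% |
| 0.4 | 0.15 | 18.8% | 11.5% | 5.1% |
| 0.5 | 0.25 | 40.9% | 22.5% | 4.9% |
| 0.6 | 0.36 | 74.2% | 42.2% | 5.1% |

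Sex as the common factor gives nearly the same result (40.3% at a = 0.5, n = 50). Across all settings run (age or sex; n = 25, 40, 50; a from 0 to 0.6) the partial test rejects in 4.8% to 5.6%. Each run adjusted for the one factor that was simulated.

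**Between-arm comparison.** Two arms of 25, both with a = 0.5 through age, were compared by the difference in Fisher z over √(2/22). The rejection rate is 5.0%, the same as at a = 0.

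**The case against.** **Covariates may be specified elsewhere.** This is a condensed article, and a full protocol or analysis plan could name them. That is possible. But the section does not leave the method open: it names the coefficient, threshold, software and display. A partial correlation is a different estimator from the one stated, so the point concerns a stated choice. The covariate step in fMRI preprocessing does not answer it, because it cannot adjust the microbiota or clinical side of an edge.

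**The size depends on assumed associations.** This stands. At 0.2 the inflation is negligible and at 0.3 it is modest. The 41% figure needs age to explain 25% of the variance in both measures of a pair, which the article's own scale calls large. Nothing in the article shows that this holds.

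**The treatment-related test is sound in this respect.** This also stands. A reader might infer that the comparison of correlations between acupuncture and sham is biased too. It is not, when the confounding is equal in the two randomised arms.

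**Change scores may be intended.** The section does not say whether baseline, Week 4 or change values are correlated. If changes are used, stable effects of age or sex on level largely cancel and the concern shrinks.

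**These analyses are exploratory.** The primary outcome, UAS7, and the clinical comparisons between arms are untouched. That limits the consequence to how the network is read.

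**Conclusion.** The concern holds as a possibility, not a certainty. As stated, the correlation analysis can draw an edge that reflects shared age or sex dependence. With 50 patients the share of otherwise unrelated pairs reaching significance runs from about 6% (both associations 0.2) through 9% and 19% to 41% (both 0.5). With 25 patients it is about 22% at 0.5. The partial version holds about 5%. All of these figures rest on assumed associations of equal strength in both measures.

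Three stronger readings are tempting but not supported:
- That the network will in fact show confounded links. The article reports no association of age or sex with any of these measures.
- That treatment arm acts as a further common cause. This would need the arms to be pooled after treatment, which the article does not state, and its between-arm test needs a coefficient within each arm.
- That head motion is ignored. Motion correction is among the preprocessing steps.

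**What to change.** In the Correlation analysis section, replace the plain Spearman correlation with a partial Spearman correlation adjusted for age and sex. Add treatment arm as a covariate only if arms are pooled after baseline. Draw the network from the adjusted coefficients.

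The change is to wording only, and age, sex and arm will be known for every patient. The cost is two degrees of freedom per correlation (48 to 46 with 50 patients, 23 to 21 within an arm of 25), or three where arm is added (48 to 45).

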##### Resting-state functional connectivity analysis

Based on the MATLAB 2013 software platform, the SPM12 software package will be used to perform the statistical analysis of brain functional connectivity. The whole-brain functional connectivity algorithm will be used to calculate the average time-series of all voxels at seed points. Next, all average time-series will be calculated individually with the Pearson correlation coefficient or the whole-brain voxel time-series. The correlation coefficient between the voxel and seed point can be obtained for each whole-brain voxel and transformed into an approximate Gaussian distribution data value using the Fisher-Z transform. Brain regions with significant statistical relationships will be identified according to a specific threshold and will be considered to have a resting-state functional connection with the seed points.

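### The correlation analysis uses one p < 0.05 threshold across many brain, microbiota and clinical pairs, and across their between-arm comparison, with no multiplicity control named

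*Protocol article*

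**What the plan says.** The section on correlation analysis covers three data domains: "The interactions between brain functional connectivity, microbiota, and clinical indicators in patients will be analyzed using MATLAB (version R2015b"), using Spearman coefficients. It adds a second layer, in which a Z test on Fisher-transformed coefficients "will be used to evaluate the differences in correlation coefficients between the acupuncture and sham acupuncture groups". Benchmarks follow: "An effect size of *r* = 0.10 is considered small (explained by 1% variance), 0.30 is medium (explained by 9% variance"), with 0.50 as large. One criterion is then given for the section: "Statistical significance is set at *p* < 0.05". The next sentence says that Cytoscape "will be employed to construct a visual network of interactions between brain functional connectivity, microbiota, and clinical indicators".

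The Microbiota analysis section lists a t-test, MetaStat and LEfSe, which "will be employed to test the significance of species composition and community structure of grouped samples". No adjustment is named there, nor anywhere else in the article. The correlation section does not call its results exploratory.

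**The concern.** A 0.05 threshold limits the error of one test. Applied to each pair in a three-domain cross-correlation, it flags about 5% of all pairs with no true association, and the number flagged grows with the number of pairs. The arm comparison repeats the problem with less power, so a larger share of what it flags will be chance.

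The article's Discussion places the acupuncture mechanism in a brain-gut-skin context and gives correlation with microbiota and symptoms a supporting part in that account. A chance edge could be read as a link in the mechanism, and a chance arm difference as an effect specific to acupuncture.

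**Working it through.** **Inputs from the article**
- Seeds: 5 (Region of interest). This is a lower bound on brain features, because the dynamic connectivity section adds means, standard deviations and coefficients of variation, and the microstate section adds further indicators.
- Clinical indicators: 8 scales (UAS7, VAS, DLQI, PSQI, HAMA, HAMD, SAS, SDS) plus IgE and CRP = 10. Adding wheal temperature, moisture, oil, elasticity, length and diameter gives 16.
- Microbiota sites: 2 (gut and skin).
- Patients: "we included 50 patients and 25 matched healthy persons in this study"; 1:1 allocation gives 25 per arm.

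**Assumptions.** The article gives no number of taxa; I take 10 per site as a low value and 50 per site as a higher one. It does not list which clinical indicators enter, so I use 10 to 16.

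**The plan's own figures.** r² = 0.10² = 1%, 0.30² = 9%, 0.50² = 25%. These reproduce. The article states no number of tests and no error rate for this analysis.

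**Number of pairs and expected false positives.** Pairs = B×C + B×M + C×M, for B brain, C clinical and M microbiota features. Expected false positives if all pairs are null = 0.05 × pairs.

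| B | C | M | Pairs | Expected false positives |
|---|---|---|---|---|
| 5 | 10 | 0 | 50 | 2.5 |
| 5 | 16 | 0 | 80 | 4 |
| 5 | 10 | 20 | 50 + 100 + 200 = 350 | 17.5 |
| 5 | 16 | 20 | 80 + 100 + 320 = 500 | 25 |
| 5 | 16 | 100 | 80 + 500 + 1,600 = 2,180 | 109 |

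Even without taxa, the chance of at least one false positive is 1 − 0.95^50 = 92% to 1 − 0.95^80 = 98%, treating the tests as independent. The arm comparison adds a set of the same size.

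**Power at p < 0.05, two-sided.** I use Fisher z with the Spearman variance 1.06/(n−3).
- Pooled patients, n = 50: standard error = √(1.06/47) = 0.150. Power is 54% for r = 0.3 and 96% for r = 0.5.
- Arm difference, 25 per arm: standard error = √(2 × 1.06/22) = 0.310. For 0.3 versus 0, 0.3095/0.310 = 1.00, power 17%. For 0.5 versus 0, 0.5493/0.310 = 1.77, power 42%.

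**Share of significant results that are false.** With t the share of pairs that are truly non-null, false share = (1−t)×0.05 / [(1−t)×0.05 + t×power]. For example, pooled, t = 0.10, r = 0.3: 0.045/(0.045 + 0.054) = 45%.

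| Truly non-null share t | Pooled, n = 50 (r 0.5 to 0.3) | Arm difference (0.5 vs 0 to 0.3 vs 0) |
|---|---|---|
| 5% | 50–64% | 69–85% |
| 10% | 32–45% | 52–73% |
| 20% | 17–27% | 32–54% |
| 50% | 5–9% | 10–23% |

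**Does the medium benchmark filter chance findings?** The critical |r| is t/√(df + t²), where t here is the 0.975 quantile of Student's t on n − 2 degrees of freedom. At n = 25 it is 2.069/√(23 + 2.069²) = 0.396, so every false edge exceeds 0.30. At n = 50 it is 2.011/√(48 + 2.011²) = 0.279. There the null probability of |r| > 0.30 is 0.0343, and 0.0343/0.05 = 69%, so about two-thirds of false edges exceed 0.30 and about 31% fall below it.

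**The case against.** The strongest reply is that the article does not say the p-values are unadjusted. A 0.05 level is compatible with adjusted p-values, and the full protocol or analysis plan, not shown here, may name a method. That stands as far as it goes: unadjusted testing is inferred from a stated threshold with no adjustment beside it. It does not remove the point. The section states a decision rule and defers nothing, and that rule, followed as written, flags about 5% of null pairs.

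Other objections limit the point:
- **Size of the network.** A reader might infer that most of it will be false. The documents do not support that. The false share depends on the unknown proportion of real associations and falls to 5–9% of pooled edges if half the pairs are real.
- **Number of tests.** Thousands of pairs would need an assumed taxon count well above 10 per site. The article also does not say that every taxon is crossed with every measure.
- **Edge rule.** That network edges are chosen by p < 0.05 is suggested by sentence order, not stated.
- **Neighbouring sections.** The resting-state section says only that "Brain regions with significant statistical relationships will be identified according to a specific threshold". This leaves a value open and is not evidence of an unadjusted rule. The t-test in the microbiota section belongs to an open-ended list and need not be meant for multivariate community structure.
- **Importance.** UAS7 is the primary outcome, and the Discussion names static connectivity, dynamic connectivity and microstate extraction as the main analyses. The correlation network supports these and is not the trial's sole evidence of mechanism.

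**Conclusion.** The point holds as a fault worth correcting in a supporting analysis. One 0.05 threshold is set for a many-pair correlation analysis and its between-arm comparison, with no multiplicity control named. The 50 to 80 brain-clinical pairs follow from the article's own lists if one feature per seed and all the counted indicators are used; the 350 to 500 total also needs the assumed 10 taxa per site. The arm comparison is the weaker part: its power is low, and at the same share of real effects more of its significant results are false. The false-share figures rest on the assumed proportion of real pairs and their assumed size, and are a range, not a forecast. The effect-size benchmark offers no protection within an arm and only partial protection in the pooled patients.

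**What to change.** In the Correlation analysis section, replace the single threshold with Benjamini-Hochberg false discovery rate control at q = 0.05 within declared families: connectivity × taxa, connectivity × clinical, and taxa × clinical, with gut and skin separate. Use the same families for the between-arm differences in correlation. Apply the same control to the taxon-level tests in the Microbiota analysis section. State that only edges surviving this control enter the Cytoscape network, and label any unadjusted result as exploratory. If a fuller plan already contains such a rule, name it in this section.

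The change takes a few sentences and a few lines of code; recruitment, data collection and treatment are untouched. The downside is fewer edges and taxa called significant. A Bonferroni rule shows the stricter extreme: over 920 pairs (16 indicators and an assumed 20 taxa per site: 80 + 200 + 640), power for r = 0.5 at n = 50 would fall from 96% to 35%. Benjamini-Hochberg is less strict, and its cut-off depends on the data.
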